### Process evaluation

In addition to the formal outcome measures, further data will be collected to allow a process evaluation to identify possible facilitators and barriers to implementation of the intervention, thus potentially influencing its effectiveness. For this purpose, caregivers’ attendance at the training sessions will be recorded and caregivers in the intervention condition will be invited to complete a short questionnaire to evaluate the intervention at 3-month and at 6-month follow-up. At the 3-month follow-up, caregivers will be asked about the activities they do at home with the person with dementia (e.g., frequency, type of activities), difficulties implementing suggestions and recommendations from the training at home and whether the person with dementia and they themselves enjoyed the activities. At the 6-month follow-up, caregivers will be asked similar questions as well as whether they still engage in the activities at home. Health care professionals who presented the intervention will be asked to evaluate the training that they have received from the research team and the strengths and weaknesses of the intervention that they encountered while training the caregivers. All evaluation questionnaires can be returned anonymously to the researchers, to encourage honest responding and prevent socially desirable responding. For process evaluation, the British Medical Research Council guidance will be used as framework (Moore, Audrey et al. [28]).

### Intervention fidelity

To assess whether the health care professionals presented the caregiver training as intended, a sample of sessions from the caregiver training will be video-recorded, with permission from the caregivers and trainers. The recording will be scored by two independent raters from the research team against a list of predetermined criteria. To assess whether the informal caregivers follow the instructions from the training at home and carry out activities with the person with dementia as intended, the activities presented at home will be scored during a home visit by the health care professional who provides the training sessions, with permission of the dyad.

### Blinding

This study is single blinded. It is not possible to blind participants or health care professionals to their allocated condition in this psychosocial intervention. However, the researchers who administer the outcome measures will be blinded to the group allocation to try to minimize the information bias effect. To reduce the risk that dyads disclose their group during the assessments, dyads are asked not to inform the researcher of the intervention until the end of the assessment. In order to still be able to ask questions about the participants’ experiences with the intervention at the 3- and 6-month follow up measurements, the researcher will be allowed to ask the condition of the participant at the end of the assessment session. In order to maintain researchers’ blinding of group allocation, the same researcher will not perform the next follow up measurement of the same dyad.

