### Setting

The MOMANT project (registered at the Dutch Trial Register; Trial ID, NTR6643) will be coordinated at the Vrije Universiteit Amsterdam and will involve organisations for care and welfare of the elderly from across the Netherlands. Recruitment of participants, and presentation of the intervention in the intervention condition, will take place at the day care centres by staff of the organisation.

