### Recruitment

Participants will primarily be recruited through health care professionals of day care centres, who are already in contact with the target population. Contact will be made through case managers and day-care coordinators, who will notify potential participants about the study and distribute written information about what participation entails. Contact details of potential participants are only passed to the research team with permission of the potential participants.

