### Randomisation

Randomisation occurs at the level of the day care centre. The allocation schedule is produced by a computer-generated random sequence. All dyads recruited at a centre will enrol in the condition to which the centre has been allocated.

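### Assessor blinding is protected dyad by dyad although allocation is by centre, so asking one dyad its condition can reveal the arm of every other dyad at that centre

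*Protocol article*

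**What the plan says.** The Randomisation section of the protocol article states that "Randomisation occurs at the level of the day care centre" and that "All dyads recruited at a centre will enrol in the condition to which the centre has been allocated".

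The Blinding section calls the study single blinded and says that "the researchers who administer the outcome measures will be blinded to the group allocation". Dyads are asked not to reveal their arm until the assessment is over. So that experiences with the intervention can be discussed at 3 and 6 months, "the researcher will be allowed to ask the condition of the participant at the end of the assessment session". The safeguard offered after that disclosure is that "the same researcher will not perform the next follow up measurement of the same dyad". Nothing is said about the other dyads of the same centre.

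The Process evaluation section separately provides a short questionnaire for intervention-arm caregivers at 3 and 6 months, and adds that "All evaluation questionnaires can be returned anonymously to the researchers".

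On recruitment, the Setting section says "Recruitment of participants, and presentation of the intervention in the intervention condition, will take place at the day care centres by staff of the organisation", and the Recruitment section says "Participants will primarily be recruited through health care professionals of day care centres, who are already in contact with the target population". The Measures section places baseline before the start of the intervention.

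**The concern.** Changing the researcher for the same dyad would work if dyads were randomised individually, because one dyad's arm would then say little about another's. Under centre randomisation one answer discloses the arm of the whole centre. The assessor may go on to the next dyad there already informed. The rotation can also hand a dyad at 6 months to a colleague who learned the arm from a different dyad at 3 months.

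At stake is the only masking that the trial claims. It matters most where the researcher's judgement enters the score: the GDS is completed in a structured interview with the caregiver.

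A related question arises at recruitment. If centre staff enrol dyads after they know their centre's arm, the two arms may enrol different kinds of dyads, and randomising centres does not prevent that.

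**Working it through.** The plan gives no figure on this point, so there is none to reproduce, and the sample size is not involved. The logic comes from reading the Randomisation and Blinding sections together; the arithmetic only illustrates the possible extent.

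**Inputs**
- m, dyads per centre: not given. The Intervention section's training-group size of 4 to 8 is used as a stand-in.
- R, assessors sharing a centre: not given; 2 to 6 assumed.
- p, the chance that the assessor asks at a visit: asking is allowed, not required, so p = 1 and p = 0.5 are shown.
- Also assumed: assessors know which centre a dyad belongs to, they are assigned at random, and all 3-month visits at a centre precede its 6-month visits. The rotation rule is fully obeyed and no dyad drops out.

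**3 months.** After k earlier visits at the centre, the assessor is still uninformed with probability (1 - p/R)^k. The informed share is

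S3 = 1 - (1/m) × Σ (1 - p/R)^k, for k = 0 to m - 1.

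**6 months.** The assessor did not make this dyad's 3-month visit. Each other dyad not yet seen at 6 months could have informed her once (probability p/R). Each one already seen at 6 months could have done so at either of two visits, which the rule gives to different people (probability 2p/R). So

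S6 = 1 - (1/m) × Σ (1 - 2p/R)^k × (1 - p/R)^(m-1-k), for k = 0 to m - 1.

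**Extremes of the assumed range**

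| p | R | m | S3 | S6 |
|---|---|---|---|---|
| 1 | 2 | 8 | 1 - 1.992/8 = 75% | 1 - 0.0078/8 = 99.9%, shown as 100% |
| 1 | 6 | 4 | 1 - 3.107/4 = 22% | 1 - 1.708/4 = 57% |
| 0.5 | 2 | 8 | 1 - 3.600/8 = 55% | 1 - 0.385/8 = 95% |
| 0.5 | 6 | 4 | 1 - 3.527/4 = 12% | 1 - 2.686/4 = 33% |

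In each S3 and S6 cell the numerator is the sum in the formula. A middle case (p = 1, R = 3, m = 6) gives 54% and 96%. A simulation of the same set-up returns the same percentages for these five cases.

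In every case shown the share is higher at 6 months than at 3 months, although the rotation rule is obeyed throughout.

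**The case against.** Several points on the other side have force.

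- **The extent is unknown.** A reader might infer that blinding fails at most follow-up visits, or at all 6-month visits. The article does not support that. It gives no number of assessors or dyads per centre, asking is optional, and the leak requires the assessor to know the dyad's centre. At 3 months the range runs well below one half.
- **The primary outcomes are only partly exposed.** The Primary outcome section describes both the EQ-5D-5L and the DQOL as self-reported, and participants are openly unblinded. Assessor masking was partial protection for them at best. The GDS is a secondary outcome and is not among the secondary analyses named in the statistical section. This stands and limits the weight of the point.
- **The question has a purpose.** A reader might call it unnecessary because a questionnaire exists. That goes too far: the questionnaire goes only to intervention caregivers, so someone must know the arm to issue it, and anonymous answers cannot be linked to a dyad. What stands is that this person need not be the outcome assessor.
- **Selection at recruitment is not established.** A reader might infer that recruiting staff cannot be blind. The statement that professionals cannot be blinded reads as being about delivering and receiving the intervention. The order of allocation and recruitment is implied by the Design and Randomisation wording but never stated, and the full protocol may settle it. Nor can a bias be sized by multiplying an assumed enrolment difference by a baseline-outcome correlation. That is the part which the planned adjustment for baseline scores is meant to remove. The Discussion also acknowledges a risk of baseline differences from cluster randomisation.

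None of this repairs the mismatch between a dyad-level rule and centre-level allocation.

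**Conclusion.** The point holds for the assessors. As written, the rotation rule cannot deliver the blinding that the Blinding section claims for it, because one dyad's answer gives the arm of the whole centre.

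Under the assumptions listed, 22-75% of 3-month and 57-100% of 6-month assessments would be made by an informed assessor if the question is always asked, and 12-55% and 33-95% if it is asked at half the visits. These figures are illustrations, not estimates for this trial. No size of bias in any outcome follows from them. The consequence is modest for the two self-reported primary outcomes and greater for the GDS.

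The recruitment part holds only conditionally: it applies if centre staff recruit after their centre's allocation is known to them, which the article suggests but does not state.

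**What to change.** **If visits are still to come**
- Delete the permission for the assessor to ask the condition.
- Collect the intervention-experience items through the process-evaluation questionnaire, issued and returned outside the assessment session, for example through the trainer or by post.
- If an assessor still learns a centre's arm, give that centre's remaining visits to another existing assessor where possible.

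**If data collection is complete** (the Discussion anticipated this by December 2021)
- Qualify the single-blind statement.
- Report how many assessments were made after the assessor had learned the centre's arm, by arm and time point.
- Run a sensitivity analysis by that flag where numbers allow, the GDS being the most relevant outcome. Few or no unflagged 6-month visits may remain; if so, report that instead of forcing the analysis.

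**Recruitment, if it follows allocation.** Identify and consent each centre's dyads and complete baseline before its allocation is disclosed. Where that is no longer possible, report approached and enrolled numbers and baseline scores by arm.

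**Cost.** A change of wording and some rescheduling of visits. Experience answers returned anonymously cannot be linked to a dyad. Rotation by centre may run out of uninformed assessors, so it is a fallback and not the main remedy. Disclosing allocation later means a short wait at each centre.

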### Ethical arrangements

This study is conducted according to the principles of the Declaration of Helsinki and all participants will give informed consent. This study has been considered by the Medical Ethics Committee of the VU University Medical Centre in Amsterdam not to fall under the Medical Research Involving Human Subjects Act. The ethics committee of the Faculty of Behavioural and Movement Sciences of the Vrije Universiteit Amsterdam has approved the study (VCWE-2017–015).

#### Consent

The nature of the research will be explained to all potential participants orally and by written information, after which dyads will have two weeks to decide whether to participate. All those who decide to take part in the study will sign an informed consent form. If people with dementia are not able to sign due to vision or writing impairments, their informal caregiver will provide consent on behalf of the person with dementia.

### Data management / statistical analysis

Data collected from participants will be stored pseudonymized, personal information will be removed and participants will identified by a number. A separate restricted-access key file will link the number with the personal information. Following completion of the study and data verification the key file will be deleted and data will be anonymised.

Data will be analysed according to the intention-to-treat principle using IBM SPSS Statistics 24 (Version 24.0; IBM Corp., 2016). All participants who entered the study will be included in the analysis according to the condition in which they had initially started. To analyse the primary outcome measures, repeated measures regression analyses (linear mixed models) will be used in order to handle clustered data and to maximise the statistical power comparing the intervention and control group at baseline, 3 and 6 months follow up. The differences between the intervention and control group at each follow-up measurement will be obtained from the linear mixed models by including time as a categorical variable and the interaction between time and the intervention group variable. Secondary analyses will examine post intervention group differences in caregivers’ sense of competence, experience of caregiving, mood, and activities enjoyed by the person with dementia using regression analyses, including baseline data as a covariate.

Analyses will be adjusted for baseline scores and potential confounding variables, i.e., factors that differ between the groups at baseline and are related to the outcome measures (at baseline) and thus might influence the impact of the intervention, e.g., demographic variables, by introducing these factors into the regression models. Baseline differences in demographic and clinical characteristics will be investigated on the cluster and individual participant level using Chi-square tests, Mann Whitney U tests, *t*-tests, and analysis of variance (ANOVA) depending on the type of variables (nominal, ordinal, interval variables).

The data collected for the process evaluation and intervention fidelity will be analysed using descriptive statistics. The data on intervention fidelity will also be used as a classification factor in the effect analysis to identify whether this makes a difference in the effect outcomes. All tests will be carried out with a 5% significance level.

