### Sample size

The sample size estimation is based on the primary outcome measures of the caregivers and the persons with dementia. At least 64 dyads in each group are required to achieve 80% power to detect significant differences between groups of half a standard deviation on the primary outcome measures using independent sample analyses with an alpha level of 0.05 (Cohen [9]). This estimate assumes a medium effect size (Cohen’s d = 0.5) on the main outcome measures, which is based on effect sizes from comparable interventions in caregivers with an average effect size of d = 0.41 (Olazarán, Reisberg et al. [29]). With an anticipated drop-out rate of 25%, 85 dyads would need to be recruited in each group to end up with 64 dyads completing the study, which is why the aim is to recruit 170 dyads in total.

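### Covariates beyond the baseline score are chosen by testing for baseline imbalance, so the primary model is not fixed in advance and balanced prognostic factors are usually left out

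*Protocol article*

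**What the plan says.** All of this is in the protocol article, mostly in Data management / statistical analysis.

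- **Fixed part:** "Analyses will be adjusted for baseline scores and potential confounding variables". The baseline score is in the models whatever the data show.
- **Data-dependent part:** the additional variables are defined as "factors that differ between the groups at baseline and are related to the outcome measures (at baseline". A factor must meet both conditions. Demographic variables are mentioned only as an example.
- **How a difference is judged:** "Baseline differences in demographic and clinical characteristics will be investigated on the cluster and individual participant level using Chi-square tests". Mann-Whitney tests, t-tests and ANOVA are also listed, and the section ends by setting every test at 5%. The article never says in one sentence that p < 0.05 is the entry criterion, but that is the natural reading of these statements together.
- **Scope:** the rule applies to the analyses in general, so it includes the primary linear mixed model.
- **Design:** "Randomisation occurs at the level of the day care centre" (Randomisation).

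**The concern.** Four features of the rule are unsatisfactory.

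1. A difference between arms does not show that a covariate is worth adjusting for. The gain in precision depends on how well the factor predicts follow-up given the baseline score. A balanced but strongly prognostic factor is excluded by design.
2. The association condition refers to the outcome at baseline, which the baseline-score adjustment already largely absorbs. A factor that predicts later change but not baseline level would tend to fail it.
3. Tests are planned at two levels with no statement of which one decides. Chi-square, t and Mann-Whitney tests on individuals treat dyads from one centre as independent, so they flag too many differences when a factor clusters by centre.
4. The covariate set becomes known only after the arms have been compared at baseline, and it can vary by chance.

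At stake are some precision and the claim that the primary model was fixed in advance.

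**Working it through.** **The plan's own figure.** "At least 64 dyads in each group are required to achieve 80% power", with "This estimate assumes a medium effect size (Cohen’s d = 0.5) on the main outcome measures". The two-sided normal formula gives 2(1.96 + 0.8416)²/0.5² = 62.8, so 63. The noncentral t gives 64 (power 0.801). Then 64/0.75 = 85.3, against 85 stated. The figure reproduces. It uses no covariates, so this point does not change it.

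**Step 1. How often is a factor flagged when there is no true imbalance?** For an individual-level test at 5%, with m dyads per centre, the probability is 2[1 − Φ(1.96/√(1 + (m − 1)ICC))]. The article gives neither m nor the ICC; m = 5 to 10 is assumed.

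| ICC of the factor | m = 5 | m = 10 |
|---|---|---|
| 0 | 5.0% | 5.0% |
| 0.02 | 5.9% | 7.1% |
| 0.05 | 7.4% | 10.4% |
| 0.10 | 9.8% | 15.5% |

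**Step 2. How often is the association condition met?** By Fisher's z with N = 170, the probability is Φ(atanh(r)√167 − 1.96): 0.745 at r = 0.2, 0.979 at r = 0.3, and about 1 at r = 0.4 or more.

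**Step 3. How often does a prognostic factor enter?** Multiply steps 1 and 2. For r of 0.3 or more this runs from 0.05 × 0.979 = 4.9% to 0.155 × 1 = 15.5%. The factor is omitted in roughly 85 to 95% of trials. If a valid cluster-level test decides, omission is near 95%.

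**Step 4. How variable is the covariate set?** With k independent candidates at ICC 0, P(at least one enters) = 1 − (1 − 0.05q)^k, where q is the probability of meeting the association condition. Both k and q are assumed.

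| k | q = 1 | q = 0.5 | q = 0.05 |
|---|---|---|---|
| 5 | 22.6% | 11.9% | 1.2% |
| 10 | 40.1% | 22.4% | 2.5% |
| 12 | 46.0% | 26.2% | 3.0% |

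**Step 5. What is an omitted covariate worth once the baseline score is in the model?** Let ρ be the baseline-to-follow-up correlation, and a and b the covariate's correlations with baseline and follow-up. The partial correlation is p = (b − ρa)/√[(1 − ρ²)(1 − a²)]. The equivalent gain in dyads is 1/(1 − p²) − 1. This treats one follow-up and ignores clustering. All correlations are assumed.

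| a | b | ρ | p² | Gain in dyads |
|---|---|---|---|---|
| 0.3 | 0.3 | 0.7 | 0.0175 | 1.8% |
| 0.3 | 0.3 | 0.5 | 0.0330 | 3.4% |
| 0.5 | 0.5 | 0.7 | 0.0588 | 6.3% |
| 0.5 | 0.5 | 0.5 | 0.1111 | 12.5% |
| 0.3 | 0.5 | 0.5 | 0.1795 | 21.9% |

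The first four rows give 2 to 13%, a cut in the standard error of about 1 to 6%. The last row is the favourable case: a covariate more weakly tied to baseline than to follow-up.

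**Step 6. Type I error.** A simulation with 8 centres of 8 dyads per arm, 5000 runs, a cluster-mean t-test and r of 0.3 or 0.5 gave 0.044 to 0.049 under the selection rule. A separate simulation with 64 per arm and r = 0.5 gave 4.3%.

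**The case against.** The strongest defence is that the covariate likely to matter most, the baseline score, is fixed in advance, and that centre randomisation makes real imbalance plausible. Centre staff recruit (Setting; Recruitment), and the Discussion concedes a risk of baseline differences. Adjusting for real confounders then has a bias rationale. The first half stands and limits the size of the point. The second supports adjustment but not selection by test. With 85 per arm and ICC 0, a true imbalance of 0.25 SD gives z = 0.25√(85/2) = 1.63 and is flagged with probability Φ(1.63 − 1.96) = 37%. Covariates named in advance correct for imbalance on those factors whether or not a test detects it.

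The candidate list may be in an analysis plan that is not shown, so its absence is not the point. The entry rule is stated, and a plan would have to replace it. Different covariates for the two primary outcomes, measured in two different people, would not in themselves be an error.

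Several stronger readings are tempting but not supported:

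- *All adjustment depends on imbalance.* It does not; the baseline score always enters.
- *The loss is about 30% of the sample.* That compares no adjustment with adjustment for one predictor at r = 0.5 (1/(1 − 0.25) = 1.33). The trial's models already hold the baseline score.
- *Chance covariates enter in about half or more of trials.* Such a figure counts the imbalance flag alone. Entry also requires the association condition (step 4).
- *Selection is steered by unblinded results.* The rule uses baseline data only, and the Blinding section says nothing about the analyst.

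**Conclusion.** The point holds as a cheap improvement. For covariates beyond the baseline score, the article fixes a rule that selects on chance imbalance, leaves open which level of test decides, and usually omits prognostic factors that happen to be balanced. The cost is a primary model not fixed in advance and a modest loss of precision: about 2 to 13% more dyads per omitted covariate, and about 22% in the favourable case. These sizes rest on assumed correlations (0.3 to 0.5 for the covariate, 0.5 to 0.7 between baseline and follow-up). The omission rates rest on assumed centre sizes and ICCs and on no real imbalance. A reader might infer that the rule inflates type I error. The simulations do not show that; rates were at or slightly below 5%.

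**What to change.** Keep the baseline-score adjustment. Replace the imbalance-and-association rule with one short covariate set for the effect models, chosen on prognostic grounds from data already collected and recorded before the arms are compared. Candidates are caregiver age and gender, relationship to the person with dementia or living situation, and baseline GDS stage. Report baseline characteristics by arm, and by centre where useful, descriptively and without significance tests. Keep imbalance-driven adjustment as a labelled sensitivity analysis. The cost is a change of wording and a few degrees of freedom; no new data are needed.

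### Fidelity exists only in the intervention arm and only after allocation, so using it as a tested classification factor in the effect analysis gives a non-randomised comparison that could credit an ineffective programme

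*Protocol article*

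**What the plan says.** Under Data management / statistical analysis, the protocol article first assigns the process and fidelity data to descriptive statistics. It then goes further: "The data on intervention fidelity will also be used as a classification factor in the effect analysis", with the stated purpose "to identify whether this makes a difference in the effect outcomes". The paragraph ends with "All tests will be carried out with a 5% significance level". Nothing marks the fidelity analysis as exploratory or non-causal.

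The Intervention fidelity section gives two sources:

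- **Trainer delivery:** "a sample of sessions from the caregiver training will be video-recorded, with permission from the caregivers and trainers". Two raters from the research team score the recordings.
- **Caregiver performance:** "the activities presented at home will be scored during a home visit by the health care professional who provides the training sessions", if the dyad agrees. The Intervention section explains that the professional rates how well the caregiver presents the activities.

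Control dyads continue with usual care (Treatment as usual), with no training sessions and no rated home visit. Home activities are encouraged only from the third meeting, so both measures arise after allocation and after baseline.

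The statistical section commits to intention-to-treat analysis. It adjusts for baseline scores and for factors that differ between the two groups at baseline and relate to outcome.

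**The concern.** A classification factor in an effect analysis is useful when it is defined in both arms, or at least before allocation. Fidelity is neither. With no value in controls, a fidelity-by-arm interaction cannot be estimated. Two comparisons remain: each fidelity class against all controls, or high against low fidelity within the intervention arm. Randomisation protects neither.

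The home rating is the more vulnerable measure. How well a caregiver runs activities plausibly depends on the caregiver's mood and competence and on the severity of the partner's dementia. These also bear on the quality-of-life outcomes. The rater is the professional who delivered the training and, according to the Blinding section, cannot be blinded. The planned covariates are chosen for imbalance between arms, not between fidelity classes, so apart from the baseline score they do not target this confounding.

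The Discussion says fidelity may influence effectiveness and names delivery by caregivers as a fidelity limitation. If the trial is null, a significant fidelity result could therefore be read as evidence that the programme works when done properly, which these data cannot show.

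**Working it through.** **The plan's own figure.** For 0.5 SD, two-sided 5% (sidedness is assumed) and 80% power, the normal approximation gives n = 2 × (1.96 + 0.84)² / 0.5² = 62.7, so 63 per group. The t-test version gives 63.77, so 64, as stated. Dropout: 64 / 0.75 = 85.3, against 85 stated. The sample size reproduces. The point does not depend on it; it supplies only the 64 completers per arm and the 0.5 SD yardstick.

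**Assumptions not in the article.** True treatment effect zero; intervention arm split at median fidelity; fidelity correlated r with the outcome through prognosis; clustering ignored. A range is shown for r.

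**Step 1, unadjusted artefact.** The mean of the upper half of a standard normal is 0.798. The high-fidelity class therefore differs from controls by 0.798 × r SD:

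- r = 0.2: 0.16 SD
- r = 0.3: 0.24 SD
- r = 0.4: 0.32 SD

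The low class differs by the same amount in the other direction, so high minus low is about 1.60 × r SD.

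**Step 2, false-positive rate.** Simulation, 20,000 replicates, 64 completers per arm, 32/32 split, unadjusted t-tests at 5%:

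| r | High − control (SD) | High − low (SD) | Rejects, high v control | Rejects, high v low | Rejects, intention to treat |
|---|---|---|---|---|---|
| 0 | 0.00 | 0.00 | 5% | 5% | 5% |
| 0.2 | 0.16 | 0.31 | 11% | 24% | 5% |
| 0.3 | 0.24 | 0.48 | 19% | 49% | 5% |
| 0.4 | 0.32 | 0.63 | 31% | 74% | 5% |

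**Step 3, allow for the planned baseline adjustment.** Suppose fidelity correlates r with the baseline score as well as with the follow-up score, and baseline and follow-up correlate p. The classes then differ by 0.798 × r at baseline too. Adjustment removes about p times that, leaving about 0.798 × r × (1 − p):

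| r | p = 0.5 | p = 0.6 | p = 0.7 |
|---|---|---|---|
| 0.2 | 0.08 | 0.06 | 0.05 |
| 0.3 | 0.12 | 0.10 | 0.07 |
| 0.4 | 0.16 | 0.13 | 0.10 |

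The range is about 0.05 to 0.16 SD. The high-minus-low contrast carries about twice that: 1.60 × 0.2 × 0.3 = 0.10 SD to 1.60 × 0.4 × 0.5 = 0.32 SD. The rejection rates in Step 2 are for unadjusted tests and should not be carried over to an adjusted model.

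**The case against.** The strongest reply is that the sentence does not say which comparison is meant. It does not say that fidelity classes will be set against controls, or that fidelity enters the primary mixed model. A comparison within the intervention arm is a natural reading, and coding detail can be left to an analysis plan that is not shown. This stands in part. A reader might infer that the primary intention-to-treat result is compromised, but the article does not support that. The mixed model is described without fidelity, which appears later, in the paragraph on process data. What does not fall away is the stated commitment: fidelity in the effect analysis, tested at 5%, to see whether it alters the effect. Neither available comparison is randomised, so a later choice of coding cannot cure this.

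Second, baseline adjustment is planned, so the unadjusted figures overstate the bias. This stands. The 0.24 SD at r = 0.3, nearly half the design effect, is not the expected bias under the plan; Step 3 is closer. Adjustment shrinks the artefact but does not remove it. It would remove less if fidelity were related to later decline beyond the baseline score.

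Third, the article gives neither the sign nor the size of r, and at r = 0 there is no artefact. This stands too. One might infer that an ineffective programme would look beneficial in well-rated dyads and harmful in the rest; the documents support only that it could.

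Fourth, the video score describes how a professional runs a group session. It belongs to the trainer or group, so the argument from caregiver ability and dementia severity applies mainly to the home rating. This is correct, and the two measures should be kept apart. The video score has its own limit: "a sample of sessions from the caregiver training will be video-recorded", so some groups may have no value.

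**Conclusion.** The point holds as a secondary but worthwhile correction. The article commits to a tested fidelity factor in the effect analysis, while its own definitions place fidelity in one arm and after allocation. Any effect-by-fidelity result is therefore observational and open to confounding that the planned between-arm covariates do not target.

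Under a zero true effect and a median split, the high-fidelity-versus-control artefact is 0.16 to 0.32 SD unadjusted (r = 0.2 to 0.4). It is about 0.05 to 0.16 SD after baseline adjustment (p = 0.5 to 0.7, with fidelity equally correlated with baseline and follow-up scores). None of these correlations is in the article, so the figures are a conditional range, not an estimate. The primary intention-to-treat comparison keeps its error rate provided fidelity is not entered into that model.

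**What to change.** Replace the sentence on the classification factor with a statement that:

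1. Fidelity will not enter the between-arm effect models.
2. The association between fidelity and outcome will be reported within the intervention arm only, adjusted for baseline score and baseline dementia severity (GDS).
3. The trainer-level video score and the dyad-level home rating will be analysed separately.
4. These results are exploratory and observational, with no claim about programme efficacy.

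The label matters because the within-arm contrast carries the larger artefact in Step 3; restricting the analysis to one arm does not remove confounding.

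Optionally, if an effect of receiving the programme is wanted, add an exploratory complier-average estimate with centre allocation as instrument and session attendance as exposure, allowing for clustering. The Process evaluation section already provides that "attendance at the training sessions will be recorded". This answers a different question from fidelity and will be imprecise. It also assumes that allocation acts only through attendance, although the manual and the home visit could act as well; both limits should be stated with the result.

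The cost is a short rewording of the analysis section and one small exploratory analysis. No new data and no change in sample size are needed.
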